### 3.4 Transfusion requirements and Transfusion stop

Maximum dose of experimental treatments administrated during the inclusion phase: 4 units of FLYP versus normal saline (enough to achieve recommended goals)

Criteria for stopping the plasma administration: in case of signs of allergy or clinical symptoms of intolerance to the treatment.

The patient will also be given normal saline as part of the usual management.

### 3.5 Description and expected duration of an individual's participation in the research

The total duration of participation for a patient in the study will be 30 days.

From the first inclusion, the sponsor must inform the competent authority and the CPP ((Ethics Committee) without delay of the effective start date of the study. In addition, the sponsor will transmit the end date of the study to the ANSM and the CPP (Ethic Committee) within 90 days.

The duration of the study is estimated at 30 months.

### 3.6 Definition and justification of the end of the research if it does not correspond to the end of the participation of the last person who takes part in the study.

The end date of the research is the end of the participation of the last person involved in the study.

The study will be prematurely stopped if unexpected serious adverse events occur. Similarly, unanticipated events or new information about the product may cause the sponsor to discontinue the study prematurely.

In case of premature termination of the study, the sponsor will transmit the information within 15 days to the ANSM and the CPP (Ethic Committee).

### 3.7 Description of the permanent or temporary stop rules

#### - of an individual's participation in research:

Each patient may withdraw from the study after the decision of the competent administrative authority, the sponsor, or the investigator, but also after the decision of a co-investigator or the patient himself in accordance with the regulations and as mentioned in the consent form.

In all cases, the investigator should document the reasons for the subject's discontinuation in the subject's medical record.

#### - of part or all of the research:

The study may be prematurely terminated in the event of unexpected serious adverse events (which may or may not require a review of the product's safety profile) or the occurrence of unanticipated events or new information about the product by the Independent Monitoring Committee (Data safety monitoring board).

### 3.8 Open-label

A blinded study cannot be performed because of the difficulties of manufacturing a placebo.

The study is therefore conducted in an open-label setting.

### 3.9 Data to be collected directly in the CRF (source data)

#### **Data collected in prehospital:**

Age,

gender

Circumstances

- ALS team delays (departure time, presentation time)
- Description of lesions, their type, and the organ injured
- Clinical parameters at ALS team arrival (HR, BP, RR, SpO2, Temperature, Hemoglobin) and their time of collection
- TREATMENT administered (FLYP or normal saline), and adverse reaction to administration (e.g., erythema), time of administration
- Filling performed: nature of products, quantity, time of administration
- Use of amines: name, dose (before/after FLYP or normal saline administration), time of administration
- Use of tranexamic acid or blood-derived medication (fibrinogen, prothrombin complex, etc.): dose, time of administration.
- Type of ventilatory support: High concentration mask, IOT-VM (FiO2 and ventilatory parameters noted), time of ventilatory management
- Chest tube +/- autotransfusion (quantity, Hemoglobin)
- Possible immobilizations, application of tourniquet or hemostatic dressing, site of tourniquet, time of application
- Transport time to the hospital
- Death before admission to hospital, date and time of death

#### **Data collected at the hospital after admission:**

- Results of blood group prior to administration of FLYP
- Results of biological samples for hemostasis analysis before and after administration of FLYP: PT, APTT, fibrinogen, CRP, coagulation factors
- Results of arterial blood gas: lactate, PaO2 (FiO2 noted), if performed
- Clinical parameters at intake (HR, BP, RR, SpO2, Temperature, Hemoglobin), time of collection
- Complete lesion assessment, time of assessment
- Severity score: ISS, IGSII, revised trauma score, TRISS
- Possible hemostasis surgery, administration of tranexamic acid, type of surgery, time of day
- Blood products transfused: name of the components transfused, time of administration
- Transfused blood derivatives: fibrinogen, ..., time of administration
- Evolution of amine requirements, administered syringe flow rate, administration time
- Evolution of hemostasis parameters
- Respiratory evolution: ventilation parameters (duration of mechanical ventilation, FiO2, etc.), ARDS-type complications
- Length of stay in Intensive care unit, mortality, date and time of death
- Length of stay, in-hospital, and 30-day mortality.

## **4 SCREENING and ENROLLMENT**

### **4.1 Inclusion Criteria**

Adult victim of a hemorrhagic shock of traumatic origin with SBP <70 mmHg or SHOCK INDEX (HR/SBP) >1.1, at a given time of prehospital medical care.

The blood pressure and heart rate criteria do not need to be simultaneous.

### **4.2 Non-inclusion Criteria**

- Refusal of the patient to participate in the research
- Patient not affiliated to a social protection system
- Age < 18 years
- Patient deprived of liberty
- Patient subject to a safeguard of justice measure
- Unrectified Legionnaire
- Pregnancy
- History of known allergies to amotosalen and psoralens
- Treatment by coagulation factor other than FLYP

- Patient in cardiac arrest

### **4.3 Exclusion Criteria**

- Patients who did not receive the final blood sample (required for the primary endpoint)
- Refusal to participate by the patient

### **4.4 Procedure for transfusion reactions**

- The participation of a patient in the study is voluntary. Any patient wishing to interrupt the experiment in which he is participating is free to do so at any time without having to justify it. The data collected will not be used in the analysis.
- The administration of the study treatment is stopped in the event of any adverse event (AE) (abnormal clinical manifestation,...), and the incriminated experimental treatment is retained. The usual management and corrective measures are continued in the field, during transport, and at the receiving hospital. A meeting of the independent monitoring committee is organized to discuss the discontinuation or continuation of the study depending on the nature of the AE.

In case of persistent consequences, the investigator will follow the patient as long as necessary.

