### **4.7 Procedures for obtaining consent from research subjects**

All selected patients who meet the inclusion criteria will be offered to participate in the study. They will be informed orally about the study and the different examinations performed by the prehospital or hospital investigating physician.

Consent must be obtained primarily from the person who is to be the subject of the research.

However, in view of article L. 1122-1-2 of the Public Health Code, if the urgency of the situation does not allow the consent of this person, it is requested from the family or the trusted person if they are present.

If consent could not be obtained prior to administration of the experimental treatment, the patient may be included by decision of the investigator, and consent will be sought from the patient as soon as his or her condition permits for the continuation of the research.

In the event that the patient dies after emergency inclusion, but before he or she is able to sign the consent to proceed, the data will be retained for the research. If possible, the investigator will inform the family.

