## 7.5 Data Safety Monitoring Board (DSMB/ CSI)

An oversight committee made up of members independent of the project will be set up:

Department of anesthesia and intensive care

Hematology-Transfusion Unit

This committee is informed during the study of any AE/SAE related to the administration of FLYP.

He is informed, in writing, by the promoter, and the information relating to the follow-up of the AEs will be transmitted to him.

It will be responsible for ruling on the causality of AEs reported by investigators during the trial. It has an advisory function when called upon by the sponsor on medical issues such as tolerance and adverse events.

The committee will decide whether or not to stop the study and whether or not to discharge the patient from the study. The recommendations concerning the continuation, possible modifications, or premature termination of the study will be transmitted to the sponsor.

This committee meets once every six months, except in particular cases.

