### **8.2 Anticipated number of people to be included in the research with its statistical justification and anticipated number of people in each research location**

- The recent literature  reports a coagulopathy rate of 50% of severely injured patients on arrival at the hospital.
- We determined that a sample size of 30 patients with coagulopathy in each group was adequate to detect a mean difference of 0.3 in INR values at hospital admission, assuming a standard deviation of 0.4, with a two-sided type I error of 0.05 and a power of 80%.

We chose this 0.3 anticipated effect size pragmatically, based on clinical judgment and the results of one previous observational study  in patients with traumatic hemorrhage of “before-after” FLYP administration

with Prothrombin Time (PT) as the endpoint, showed a significant improvement in PT “after” FLYP. A total of 124 patients were required to observe a statistically significant difference.

Assuming an incidence of coagulopathy of 50%, this resulted in 60 subjects per group. Given the a priori loss of 10% due to lack of informed consent, we rounded the target size of each group to 70 and included a total of 140 patients. To consider a median difference of 0.3 in INR values instead of mean difference, the sample size needs to be approximately 25 coagulopathic patients per group, for a total of 120 patients, based on the same alpha and beta risk assumptions. INR values will be presented according to their median (IQR) and by a three-category variable with cutoff values of 1.2 and 1.5.

[figure not shown]

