## **8.7 Patients included in the analysis**

Analysis populations will be :

- in intention-to-treat for the safety outcome (ITT: taking into account all randomized patients)
- in modified intention-to-treat analysis for the primary outcome (mITT: taking into account all randomized patients except those for which the eligibility criteria were not met)
- in Per-Protocol (PP: taking into account patients randomized but excluding the patients for which the eligibility criteria were not met and those who were declared free from any haemorrhagia after the hospital check-up.

All statistical analyses will be performed with STATA® software 14.0 or an updated version for Windows (STATA CORP LLC, College Station, Texas, USA).

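### Withdrawal deletes a patient's data while death before consent keeps them, so inclusion in the 30-day survival analysis depends on being alive when asked, and the rule contradicts the all-randomised safety population.

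*Combined protocol and SAP*

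**What the plan says.** - **Protocol 4.4.** A patient may stop taking part at any time without giving a reason. The rule for the data is: "The data collected will not be used in the analysis".
- **Protocol 4.3.** One of the two exclusion criteria is "Refusal to participate by the patient". The other is a missing final blood sample. Refusal is already a non-inclusion criterion in 4.2, so its listing in 4.3 reads as refusal after inclusion.
- **Protocol 4.7.** The patient is asked first. If urgency prevents this, "it is requested from the family or the trusted person if they are present". Failing both, the investigator may include the patient, and "consent will be sought from the patient as soon as his or her condition permits for the continuation of the research". If a patient included this way dies "before he or she is able to sign the consent to proceed, the data will be retained for the research".
- **SAP 16.5, analysis populations.** The primary and secondary outcomes use all randomised patients except those with an exclusion criterion (mITT). Safety uses all randomised patients. Protocol 8.7 agrees on safety: "in intention-to-treat for the safety outcome (ITT: taking into account all randomized patients". However, it defines the mITT by unmet eligibility criteria, not by exclusion criteria.
- **SAP 16.5, deviations, and SAP 16.6.** Missing or incomplete consent is a protocol deviation, screened for in the intention-to-treat population. Withdrawals are tabulated by whether consent to follow-up and to data collection continues.
- **SAP 16.8.** Multiple imputation is confined to mITT patients.
- **Protocol 8.2.** Non-consent is expected and budgeted for: "Given the a priori loss of 10% due to lack of informed consent".

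**The concern.** Two patients can be treated alike under emergency inclusion. One dies before being able to sign and stays in the dataset. The other recovers enough to be asked, declines, and is deleted. Retention thus depends on survival to the consent conversation, and survival to day 30 is itself a secondary endpoint. The trial is open-label, so the arm and any reaction may be known when the patient decides. Refusal may then differ by arm. Imputation cannot repair this, because the deleted patients lie outside the set that is imputed.

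For harms the problem is a contradiction. The safety population is every randomised patient, yet 4.4 forbids use of a withdrawn patient's data. If 4.4 prevails, a patient who reacts and then withdraws is lost from the safety count. If 8.7 prevails, 4.4 is not followed. Unless this is settled beforehand, who counts could be decided once arm and outcome are known.

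**Working it through.** **1. The plan's own figures.** Inputs from protocol 8.2: difference 0.3, SD 0.4, two-sided alpha 0.05, power 80%, coagulopathy 50%, consent loss 10%.
- n per group = 2 × (1.960 + 0.842)² × (0.4/0.3)² = 27.9, so 28, or 29 with the t distribution. The plan says 30, which is reproduced to within 2.
- 30/0.5 = 60. Then 60/0.9 = 66.7, so 67, which the plan rounds to 70.
- A 10% loss from 70 is 7 patients, leaving 63 per arm.

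**2. Mortality within one arm.** Let p be true 30-day mortality and d the share of the arm removed. If everyone removed is alive at day 30 and every death is kept, observed mortality = p/(1 − d). The documents give a death rate of around 50% (7.2.2) and about 40% with coagulopathy (1.2).

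| True mortality | Deaths of 70 | Kept | Observed |
|---|---|---|---|
| 50% | 35 | 63 | 35/63 = 55.6% |
| 40% | 28 | 63 | 28/63 = 44.4% |

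At 50% mortality, this means that 7 of 35 survivors (20%) refuse.

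**3. Comparison between arms.** The documents give no split of refusals by arm, so the splits below are assumptions.
- *Equal loss, no treatment effect:* both arms shift together and the risk ratio stays at 1.00.
- *Equal refusal among survivors, true effect 40% v 50% (risk ratio 0.80):* with refusal probability q, observed mortality = p/[p + (1 − p)(1 − q)]. At q = 0.10 the arms read 42.6% v 52.6%, ratio 0.81. At q = 0.20 they read 45.5% v 55.6%, ratio 0.82. The attenuation is slight.
- *The same 14 refusals split 10 v 4, no treatment effect:* at 50% mortality, 35/60 = 58.3% v 35/66 = 53.0%. At 40%, 28/60 = 46.7% v 28/66 = 42.4%.
- *Loss of 5% v 15%, no treatment effect:* the ratio is 0.85/0.95 = 0.895, or 1.118 in the other direction. The false difference is 5.0 points at 40% mortality and 6.2 at 50%. In 200,000 simulated trials of 70 per arm, a pooled two-proportion z test rejected in 8.7% and 10.8% of trials, against a nominal 5%.

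**4. A loss in the other direction.** The missing-sample criterion in 4.3 also removes patients who die before the arrival sample. As an illustration (assumed), if 7 of 35 deaths lack the sample and 7 survivors refuse, mortality reads 28/56 = 50.0%, the true value.

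**5. Arrival INR.** Assume that patients who die have a mean INR higher by g = 0.2 to 0.6, with mortality of 40% to 50%.
- Equal 10% loss shifts both arms by g × p × (1/0.90 − 1), from 0.2 × 0.4 × 0.111 = 0.01 to 0.6 × 0.5 × 0.111 = 0.03.
- Loss of 5% v 15% opens a gap of g × p × (1/0.85 − 1/0.95) = g × p × 0.124, which is 0.01 to 0.04. The target difference is 0.3.

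**6. Safety.** No arithmetic applies. Protocol 8.7 and SAP 16.5 admit every randomised patient, SAP 16.5 looks for missing consent inside that population, and SAP 16.6 recognises degrees of withdrawal. Protocol 4.4 recognises one degree only and deletes the data. These cannot all be followed.

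**The case against.** The strongest reply is that the direction of the bias is not established, and this stands. A reader might infer that non-consent removes only people who survive, so that mortality must be overstated. But a patient who refuses early can still die by day 30, a relative may be approached before the outcome is known, and the missing-sample criterion removes early deaths. Protocol 8.7 also defines the mITT differently from the SAP, so removal of later refusers rests on the SAP wording and on 4.4.

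Other stronger readings also lack support:
- *Most patients are treated first and asked later.* Protocol 4.7 gives no proportion and puts deferred consent last.
- *The monitoring committee offers a removal route in the FLYP arm alone.* Section 7.5 does let the committee decide "whether or not to discharge the patient from the study", but 3.7 allows withdrawal by sponsor or investigator in either arm. No section deletes data after such a decision; the sentence in 4.4 follows the patient's own wish.
- *Reactions will be undercounted.* The separate item in 4.4 on adverse events deletes nothing, and serious-event reporting runs independently (7.2). An undercount follows only if the discard sentence overrides 8.7.
- *The primary endpoint is materially biased.* Step 5 does not show this.

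It is also fair that the 10 v 4 difference, about 5 points, is only some 0.6 of its standard error (about 9 points), on a secondary endpoint. SAP 16.6 already tabulates withdrawals and reports losses to follow-up by arm. That makes losses visible but does not restore the data or settle which rule governs.

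**Conclusion.** The concern holds as a defect in the stated data rules. Retention depends on being alive when asked and can depend on arm. Imputation as planned cannot recover the patients removed, and 4.4 contradicts the safety population.

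The size is conditional. Mortality of 55.6% for a true 50%, or 44.4% for a true 40%, assumes that the whole 10% loss falls on day-30 survivors and that nothing else is excluded. The net direction is unknown. No between-arm bias arises when refusal is equal and treatment has no effect, and with a true effect the attenuation is small. A false difference of roughly 4 to 6 points needs unequal refusal of the assumed sizes. Arrival INR probably moves by a few hundredths at most. For harms the finding is an unresolved conflict, not a demonstrated undercount.

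**What to change.** Reconcile protocol 4.3, 4.4, 4.7 and 8.7 with SAP 16.5 and 16.6 before analysis, using one definition of the mITT. Replace the discard sentence in 4.4 with three separate events:

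- **(a) Study treatment is stopped:** follow-up and analysis continue.
- **(b) Further follow-up is declined:** data up to that date are kept and analysed, including arrival INR and adverse events. Survival is censored at last known vital status.
- **(c) The patient objects to use of data already collected:** data are removed as the consent rules require, and these patients are counted by arm in the CONSORT diagram.

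Limit refusal in 4.3 to (c). State that safety covers all randomised patients except (c).

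Add a sensitivity analysis of 30-day survival with best- and worst-case bounds for (c), including opposite extremes in the two arms. Counting every objector as a day-30 survivor would not be valid, because being alive when asked is not being alive at day 30. For scale, 7 objectors in an arm of 70 with 35 recorded deaths give bounds of 35/70 = 50% and 42/70 = 60%.

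The cost is wording in the protocol, SAP and information sheet, plus one extra analysis. Sample size is unchanged. The data-use wording needs ethics committee approval and must fit the consent rules, which are not fully visible in the documents reviewed. Patients keep the right to object.

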### **4.5 Hospital care follow-up if the research is stopped**

The medical care of the persons planned at the end of the research or in case of premature termination is carried out within the receiving hospital or in another hospital structure after transfer according to the usual care carried out in the care structures.

### **4.6 Arrangements for monitoring individuals involved in research based on, among other things, non-clinical data, including the duration of monitoring and follow-up procedures, and procedures for the medical management of individuals involved in research in the event of an emergency**

In the event of an emergency, research subjects are managed and monitored by a prehospital and then hospital care team according to the department's usual protocols until they are discharged from the department (death, return home, other care facilities), and if necessary, until the resolution of the SAE.

### **4.7 Procedures for obtaining consent from research subjects**

All selected patients who meet the inclusion criteria will be offered to participate in the study. They will be informed orally about the study and the different examinations performed by the prehospital or hospital investigating physician.

Consent must be obtained primarily from the person who is to be the subject of the research.

However, in view of article L. 1122-1-2 of the Public Health Code, if the urgency of the situation does not allow the consent of this person, it is requested from the family or the trusted person if they are present.

If consent could not be obtained prior to administration of the experimental treatment, the patient may be included by decision of the investigator, and consent will be sought from the patient as soon as his or her condition permits for the continuation of the research.

In the event that the patient dies after emergency inclusion, but before he or she is able to sign the consent to proceed, the data will be retained for the research. If possible, the investigator will inform the family.

**PREHOSPITAL SETTING = First attempt to recover consent form**

[figure not shown]

Rules for the obtention of patient's consent, under the French legislation and approved by the ethics committee

#### 4.8 Concurrent participation in another research study and expected exclusion period at the end of the study

The patient is not a priori scheduled to participate in another interventional study during the time of study participation. There is no exclusion period.

### 5 TREATMENTS ADMINISTERED

#### 5.1 FLYP

##### 5.1.1 Indications

Its indications are :

- moderate, poorly progressive or controlled hemorrhage (guided primarily by laboratory tests with a patient/control prothrombin time ratio > 1.5)
- hemorrhagic shock and situations at risk of massive bleeding.

[figure not shown]

### 5.1.2 Packaging of the product

The freeze-dried plasma is secured by treatment with amotosalen.

It is vacuum-packed in a 200 ml bottle.

An instruction leaflet, a prescription-delivery-clinical and biological monitoring form systematically accompany the product in its packaging.

